## Abstract

Preventive care to address chronic disease risk behaviours is infrequently provided by community mental health services. In this cluster-randomised controlled trial, 12 community mental health services in 3 Local Health Districts in New South Wales, Australia, will be randomised to either an intervention group (implementing a new model of providing preventive care) or a control group (usual care). The model of care comprises three components: (1) a dedicated ‘healthy choices’ consultation offered by a ‘healthy choices’ clinician; (2) embedding information regarding risk factors into clients’ care plans; and (3) the continuation of preventive care by mental health clinicians in ongoing consultations. Evidence-based implementation strategies will support the model implementation, which will be tailored by being co-developed with service managers and clinicians. The primary outcomes are client-reported receipt of: (1) an assessment of chronic disease risks (tobacco smoking, inadequate fruit and vegetable consumption, harmful alcohol use and physical inactivity); (2) brief advice regarding relevant risk behaviours; and (3) referral to at least one behaviour change support. Resources to develop and implement the intervention will be captured to enable an assessment of cost effectiveness and affordability. The findings will inform the development of future service delivery initiatives to achieve guideline- and policy-concordant preventive care delivery.

## 1. Introduction

Mental health conditions are a clinically diagnosable disorder that impacts a person’s thinking, feeling, behaviour or mood [1]. The term covers a range of diagnoses (such as mood disorders, anxiety disorders and psychoses and severities) and may lead to people presenting to a mental health service for treatment [1]. A higher prevalence of key chronic disease risk factors (tobacco smoking, inadequate fruit and vegetable consumption, harmful alcohol use, physical inactivity and overweight/obesity [2]) contributes substantially to the greater burden of chronic disease morbidity and mortality [3] experienced by people with a mental health condition. Internationally, the median gap in life expectancy is 10 years, which is evident across the range of mental health conditions [4]. In Australia, the average gap in life expectancy for people receiving treatment from a psychiatric facility, compared to the general population, is 12–16 years, with approximately three quarters due to potentially preventable chronic diseases, such as cardiovascular disease and type 2 diabetes [5]. The need to redress the physical health inequity experienced by people with a mental health condition, and specifically the higher prevalence of chronic disease risk factors, is a recognised priority internationally [6] and in Australia [7].

Clinical practice guidelines [8] and policies [9] direct health services, including mental health services, to provide evidence based ‘preventive care’ to support clients in making positive changes to chronic disease risk behaviours [10,11,12,13]. In Australia, community mental health services, which provide support to the large majority of people who receive specialist mental health treatment, represent a key opportunity to provide preventive care to a large proportion of people with a mental health condition and particularly those with severe mental ill-health [14]. Evidence-based frameworks to guide such care include the ‘AAR’ framework: *assessment* of chronic disease risk factors, *advice* to modify identified risks, and *referral* to support services, providers or groups to provide ongoing behaviour change support [15,16,17]. Preventive care can also include broader elements of assisting clients to change, such as goal setting, motivational interviewing, agency building and follow-up support [18,19], aligning with the frequent and often extended period of engagement with clients that typifies the support provided by multidisciplinary community mental health teams. Research has found that community mental health clinicians do consider that providing preventive care is an important part of their role [20]. Despite this, a meta-analysis of 38 studies indicated that preventive care was infrequently provided by mental health services, including community mental health services [21]. Further, a number of barriers to the provision of preventive care in this setting have been identified, including lack of knowledge regarding risk factors and confidence in assessing them, inadequate time to undertake a comprehensive risk assessment and advice provision within a typical consultation, and a perceived lack of referral options [22].

Research has been conducted to examine the effectiveness of interventions to increase preventive care provision in mental health settings. A recent systematic review by Fehily et al. (2020) identified twenty studies (of any design with a comparison group) with such an aim [23]. Of the included studies (*n* = 20), most examined smoking only (*n* = 14), with few targeting other risk behaviours (*n* = 6). Effective intervention strategies (defined as demonstrating a significant increase in preventive care in at least two studies) were identified within two categories of the Effective Practice and Organisation of Care Taxonomy [24]: (1) delivery arrangements: changes in who is responsible for care provision or how, when or where care is delivered (including embedding additional staff with specialist roles); and (2) implementation strategies: strategies to influence the behaviour of organisations or clinicians, or use of health services by clients (including clinician training, educational materials, health information systems, local consensus processes, authority and accountability, and reminders).

Embedding an additional provider in a mental health service with a dedicated preventive care role is a delivery arrangement with the potential to overcome the aforementioned barriers. The above systematic review identified that this approach led to significant increases in client receipt of preventive care [23], and additional studies have reported this approach increased the provision of broader physical health care (e.g., metabolic outcomes, self-examination, and access to primary medical care) [25]. Both clients [26] and mental health clinicians [27] show support for such an approach, though have indicated the importance of it being coordinated with usual care provision and not adding to the existing fragmentation of physical and mental health care delivery [26]. In our first study exploring this model of care—and the only published study to do so with a focus specifically on multiple key chronic disease risk factors—we undertook a randomised controlled trial with clients (*N* = 811) of one New South Wales (NSW) community mental health service. Clients were randomised to receive either usual care, or usual care plus the offer of an additional consultation with a ‘preventive care clinician’ [28]. At 1-month follow-up, clients in the intervention condition reported significantly greater increases in the receipt of assessment for all four risk factors (*p* < 0.001), advice for all applicable risks (*p* = 0.019), and offers of referrals to applicable telephone support services (*p* = 0.004), as compared to participants receiving usual care. The trial demonstrated that comprehensive AAR care for multiple risks was feasible to offer and deliver in a dedicated consultation within this setting, and further that this could be achieved at a low per-client cost [29]; additionally, it was viewed by clients as acceptable [30]. However, a limitation of the model was noted to be the risk of perpetuating the problematic separation of responsibilities and roles in providing care for physical and mental health (between the preventive care clinician and other mental health clinicians). In this trial, other than a summary recorded by the specialist clinician in the electronic records, the additional consultation was not integrated into clients’ ongoing care. Furthermore, there was no defined role for mental health care managers to continue or reinforce the preventive care provided by the specialist clinician.

Therefore, whilst the findings were largely positive, further research is needed to address this limitation and develop the model of care, specifically with respect to integrating the additional consultation within routine service provision, and identifying implementation strategies that can effectively support services and clinicians. Cochrane systematic review evidence supports the effectiveness of various implementation strategies in increasing preventive care in general health settings, including leadership and consensus processes [31], enabling systems, training [32], audit and feedback [33], and client activation [34]. Only one study has explored the effectiveness of implementation strategies in increasing preventive care provision by clinicians in mental health settings for the key chronic disease risk behaviours of tobacco smoking, inadequate fruit and vegetable consumption, harmful alcohol use and physical inactivity [35]. In a multiple baseline trial (*n* = 19 community mental health services), a suite of the implementation strategies supported by the Cochrane review evidence were trialled to support preventive care provision. The results indicated a significant increase for only one of 16 preventive care outcomes, and it was suggested that the use of generic implementation strategies that were not tailored to the specific context of mental health settings may have contributed to the limited effect [35].

To address this evidence gap, the present study will assess the effectiveness of a model of care in increasing the provision of preventive care for key chronic disease risk factors (tobacco smoking, inadequate fruit and vegetable consumption, harmful alcohol consumption, physical inactivity, and overweight/obesity) in community mental health services. The model consists of three components: (1) offering clients a preventive care consultation (content framed around the AAR framework) with a dedicated ‘healthy choices’ clinician (HCC); (2) embedding information regarding client chronic disease risks into the existing care management plan; and (3) the continued provision of preventive care by mental health clinicians in ongoing consultations. Strategies to support the implementation of the model of care draw on evidence-based implementation strategies [31,32,33,34], tailored to the service settings through co-development with managers and clinicians to consider the clinical, professional and organisational factors of community mental health service delivery. The primary outcomes are client-reported receipt of preventive care (elements within the AAR framework). Client risk factors and attempts to change risk factors, confidence, and readiness to change are assessed as secondary outcomes. Cost and cost-effectiveness of the intervention will also be quantified.

The study was registered with the Australian and New Zealand Clinical Trials Registry: ACTRN12621000922875 (date registered: 15 July 2021). It was approved by the Hunter New England Human Research Ethics Committee (Ref: 2020/ETH03234) and the University of Newcastle Human Research Ethics Committee (Ref: H-2021-015), and authorised for conduct by the Central Coast (Ref: 2021/STE00265) and Mid North Coast (Ref: 2021/STE00264). Supplementary-Table S1 contains the Standard Protocol Items: Recommendations for Intervention Trials (SPIRIT) checklist, noting where all recommended items were reported in this protocol.

### 2.2. Randomisation and Blinding

Twelve services will take part in the study. Based on the number of services available in each LHD, this will include six from one LHD, three from the second, and three from the third. An independent statistician will use a computerised random number function to randomly allocate services in a 1:1 ratio to either the intervention or control condition within the strata (three LHDs). Constrained randomisation will be used to ensure balance between the intervention and control groups in terms of service characteristics: size (based on client numbers; 2 levels; cut off point of 1500), structure (2 levels: single site versus multisite), and rurality (determined by service postcode; 2 levels: major city vs. inner/outer regional [40]). Following the randomisation, researchers, services, clinicians, and clients will not be blind to allocation. Statisticians undertaking outcome analyses will be blinded to group allocation. Interviewers collecting data from clients will be blinded to group allocation (with the exception of the end of the follow-up survey where intervention participants will be asked additional questions regarding the intervention).

### 2.3. Participant Eligibility and Recruitment

#### 2.3.1. Community Mental Health Services

Agreement for an LHD to participate in the trial was sought from the mental health director for each LHD. Community mental health services within each LHD were eligible to take part if they were not currently engaged in other research with the team. The identification of discrete services (‘clusters’) to be included in the trial was then determined through an assessment of management structure (e.g., services having their own manager), size (annual client throughput and number of clinical staff) and structure (single site or multisite). Within two LHDs, smaller sites that came under one overarching manager were treated as one service for this trial (considered multisite services). In the other LHD, it was not possible to ensure that different services had unique managers, as two managers oversee staff across multiple locations, including both intervention and control services. However, the services have discrete clinicians and clients.

#### 2.3.2. Clients

Participants will be clients of the participating services. Participation in data collection will be independent of any care provided by the service. Data collection via computer-assisted telephone interviews (CATI) will be conducted through cross-sectional surveys (Figure 1) with eligible clients (outlined below).

##### Cross-Sectional Surveys

Clients of intervention and control services who are 18 years or older and attended at least two consultations in the previous 9 months will be eligible to be randomly selected (from service records) for participation in the two independent cross-sectional surveys (baseline and follow-up). An average of 120 eligible clients per service will be randomly selected from the electronic health service records during both the baseline and follow-up period (720 intervention group; 720 control group). These clients will be mailed an information statement by the service describing the nature of the study and providing an opportunity to opt-out by calling a toll-free number. Clients who do not opt-out will be contacted 2 weeks later by trained telephone interviewers within a NSW health service CATI team to assess the additional eligibility criteria (English speaking (due to practical constraints); mentally and physically capable of responding to survey items; and does not report having an eating disorder as their primary mental health condition) and seek their consent to participate. Clients could be randomly selected as part of both baseline and follow-up samples, with consent to take part in each survey sought independently.

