##### Cohort Client Follow-Up (Nested Study)

A random selection of eligible client participants (100 from each group) will form a cohort sub-sample who will be contacted via telephone and invited to complete the cohort follow-up survey. Eligible clients will be those who completed the baseline survey and, at that time, consented to be contacted regarding the cohort follow-up; and either (1) were offered the healthy choices consultation (if in the intervention group) or (2) had at least one mental health consultation in the preceding 9 months (if in the control group).

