#### 2.4.2. Model of Preventive Care

The model of care consists of three key components, which will be delivered to clients of mental health services during the 9-month intervention period (see Figure 2 for summary):‘Healthy choices’ consultation

A 40 minute consultation dedicated to addressing chronic disease risk factors and provided by a ‘Healthy Choices Clinician’ (HCC) will be offered to adult clients. The consultation will be framed around the evidence-based AAR framework [15,16,17] for key chronic disease risk factors (smoking, nutrition, alcohol, physical activity, and overweight/obesity) and collaboratively setting behaviour change goals with the client. The consultation will incorporate evidence-based behaviour change techniques, such as motivational interviewing [41]. The HCC could have a range of professional backgrounds (e.g., occupational therapist, dietician, nurse, and social worker) and will have expertise in health behaviour change strategies. The fractional HCC appointment (hours per week) required in each service will be determined through co-development (proportional to number of clients and staff). HCCs will complete training in intervention delivery according to a manualised protocol. The consultation, tailored to each client, will include:Assessment: Clients will be asked about their current engagement in risk factors, with risk status determined in accordance with the Australian National Health and Medical Research Council Guidelines (Table 2) [42,43,44,45,46].Brief advice and goal setting: Information will be provided regarding how the client’s risk factors compare to Australian guidelines. Tailored motivational interviewing strategies will be used to foster client desire to change their risks and build agency. Clients will be encouraged to identify at least one health improvement goal in line with their risk status and/or desired areas for improvement.Referral: Clients will be offered referrals to services that provide behaviour change support, based on their risk status [42,43,44,45,46] and/or their identified health improvement goals. This could include referral to services, such as state-level telephone services (e.g., the NSW Quitline [47] and NSW Get Healthy Information and Coaching service [48]) and local providers (e.g., GP, dietician, support groups, and walking groups).

ii.Chronic disease risk information embedded in the care plan

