#### 2.6.2. Secondary Trial Outcomes

##### Client Receipt of Preventive Care

The secondary outcomes regarding preventive care are client-reported receipt of the individual elements of preventive care for the individual AAR elements for each chronic disease risk behaviour and weight, and conversations with their mental health clinician about their behaviour change goals. Clients will be asked to report their receipt of each preventive care element (assessment, advice and referral) for each individual risk factor (tobacco smoking, inadequate fruit and vegetable consumption, harmful alcohol consumption, physical inactivity, and overweight/obesity) from their mental health service in the previous 9 months (total of 15 items). Participants will also be asked whether their mental health clinician spoke to them in the preceding 9 months about their goals for behaviour change (yes/no/do not know).

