### 2.8. Analysis

Mixed effects logistic regression models will compare the primary outcomes and secondary practice change outcomes (preventive care receipt) between the intervention and control groups at the post-implementation follow-up, adjusting for clustering by service with a service level random intercept. The models will also adjust for potential confounders, including baseline prevalence of preventive care, age, gender, psychiatric diagnosis, and length of time in treatment, as well as LHD as fixed effects. Analyses will be carried out on an intention to treat basis.

In the cohort sub-study, generalised mixed effects regression models will determine the change over time (baseline to 9-month cohort follow-up) in the intervention compared to control participants in the measures relating to client behaviour change: smoking status (yes/no), serves of vegetables per day, serves of fruit per day, number of standard alcohol drinks per week, minutes of moderate and vigorous physical activity per week and body mass index (BMI). Models will adjust for clustering by service and potential confounders as well as LHD. Descriptive analyses will be used to report the remaining measures.

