Clinical support personnel	The HCC embedded within each service is funded for 9 months by the trial, employed by the LHD as a member of the service. In addition to client care delivery, the HCC also provides support and training to clinicians. Implementation support officers (research team members; one allocated to each LHD) will regularly contact the HCC to support them in this role.	Preferred clinical background and experience of the HCC and the title for the position. The fractional HCC appointment (hours per week) required in each service, proportional to number of clients and staff. Additional duties (e.g., completion of existing tools and involvement in training). Frequency and mode of Implementation Support officer contact with HCC.
Leadership and consensus processes	Managers communicate support for the new model to all clinicians and reinforce its alignment with state policy and the LHD’s strategic directions. An advisory group for each LHD is established, with representation of the research team, directors, and service managers to oversee implementation, and to monitor and provide feedback throughout.	Avenues for leaders to communicate support for the new model of care to clinicians (e.g., email distribution lists, videos, flyers, and staff meetings). Training or resources to provide managers to support them in facilitating implementation. Advisory group members and frequency

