Enabling systems	The HCC records a summary of each ‘healthy choices’ consultation in the electronic medical record system. Content regarding risk behaviours, goals for change, and referrals offered and/or accepted is integrated into the existing care management plan that is part of routine mental health care delivery. The review of the plan is incorporated within the regular team clinical review meetings where the needs and progress of individual clients are discussed. The HCC attends clinical review meetings, contributing to discussions of how plans are incorporated in routine care and offering additional support or advice to clinicians as required.	Detail of where/how health choices consultation recorded in electronic medical record. Other changes to electronic systems that may support implementation, e.g., a process to streamline referrals, such as a referral template or compilation of available referral services, and a template for the HCC to record detail of the ‘healthy choices’ consultation content. Formal and informal communication channels between the HCC and clinicians regarding care plan content (e.g., the HCC notifying clinicians when new content is added to care plans). Regular agenda items in clinical review meetings for the HCC to discuss.
Clinician education and training	Training sessions and resources are provided regarding the importance of addressing risk factors for both physical and mental health, risk guidelines and referral services. Clinicians are upskilled in strategies to support client behaviour change, including motivational interviewing, setting and reviewing, e.g., goals, and identifying and addressing barriers. Training is provided in the processes to implement the model of care, such as in scheduling and facilitating client attendance of the ‘healthy choices’ consultation and checking and updating the care plan.	Frequency, length and mode (online and face-to-face) of training for HCCs and clinicians. It is expected that the HCC has a role in training delivery for clinicians. Type of training (interactive, roleplays, self-paced, and recorded webinars). Useful resources for training (manuals, evidence guides, ‘how to’ guides). When training is held (e.g., during existing training opportunities or scheduled as a separate training session).

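### The follow-up survey entry rule does not exclude the healthy choices consultation from the two qualifying consultations, so eligibility can depend on allocation

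*Protocol article*

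**What the plan says.** All places are in the protocol article.

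- **Entry rule (Cross-Sectional Surveys).** Adult clients who "attended at least two consultations in the previous 9 months will be eligible to be randomly selected (from service records" form the sampling frame. The wording is the same for both arms and for both surveys, and neither the type of consultation nor the provider is specified.
- **Tested care (2.4.2).** "A 40 minute consultation dedicated to addressing chronic disease risk factors and provided by a" healthy choices clinician (HCC) is offered in intervention services only, over 9 months.
- **Provider (Table 1, Clinical support personnel).** The HCC is "employed by the LHD as a member of the service".
- **Record (Table 1, Enabling systems).** The HCC enters a summary of each healthy choices "consultation in the electronic medical record system". Exactly where and how it is recorded is left to co-development.
- **Outcome window (Client Receipt of Preventive Care).** Clients report the care elements received "from their mental health service in the previous 9 months (total of 15 items". The primary outcomes combine the same elements across risks.
- **Cohort rule (Cohort Client Follow-Up), for contrast.** A control client must have "had at least one mental health consultation in the preceding 9 months (if in the control group". Here the type of consultation is named.
- **Covariates (2.8).** The models adjust for confounders "including baseline prevalence of preventive care, age, gender, psychiatric diagnosis, and length of time in treatment", and for Local Health District (LHD). The number of usual consultations is not listed, although section 2.6.3 has a 9-month appointment count extracted from the records.

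**The concern.** The follow-up sample is drawn after the intervention, and its 9-month look-back largely coincides with the intervention period. Read literally, the rule lets a contact that exists in one arm only count towards entry. Take two clients with one usual consultation each. The one in an intervention service who also attends the HCC reaches two and can be sampled. The one in a control service stays at one and cannot.

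This would be selection after randomisation. Everyone admitted by this route has attended the consultation designed to deliver assessment, advice and referral, which are the three primary outcomes. Analysis by allocated group does not remove the problem, because it arises in who is sampled. Nor do the listed covariates, since length of time in treatment is not the number of usual visits. The cost-effectiveness analysis (2.9) uses the same primary outcomes and would carry any inflation forward.

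**Working it through.** **1. The plan's own figure.** Section 2.7 gives 180 clients per arm, intraclass correlation 0.05, 20% rising to 45%, type 1 error 0.017 and 80% power. With 6 services per arm there are 30 clients per service.

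- Design effect = 1 + (30 − 1) × 0.05 = 2.45
- Effective n per arm = 180 / 2.45 = 73.5
- Power (two-sided, normal approximation) = 0.81, so the stated 80% is reproduced. Sidedness is not stated; two-sided is assumed.

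The entry rule plays no part in this calculation, so changing it leaves sample size and power as planned.

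**2. Who is admitted only through the tested consultation.** Let s be the share of clients with exactly one usual consultation, among those with one or more, and h the share of these who attend the HCC. The intervention frame then holds (1 − s) regular clients plus s × h extra clients:

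share = s·h / ((1 − s) + s·h)

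**3. Shift in the intervention-arm rate.** Let p₁ be the reported receipt among the extra clients and p_rest the receipt in the rest of the frame:

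shift = share × (p₁ − p_rest)

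The documents give none of s, h and p₁. I assume s of 10–25%, h of 20–40% and p₁ = 80%. For p_rest I use the design target of 45%. As a check, I also derive it by giving regular clients the same uptake h, with 80% receipt among attenders and 20% among others: p_rest = 0.80h + 0.20(1 − h).

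| s | h | share | shift, p_rest = 45% | derived p_rest | shift, derived p_rest |
|---|---|---|---|---|---|
| 0.10 | 0.20 | 0.020/0.920 = 2.2% | 0.8 points | 32% | 1.0 points |
| 0.15 | 0.30 | 0.045/0.895 = 5.0% | 1.8 points | 38% | 2.1 points |
| 0.25 | 0.40 | 0.100/0.850 = 11.8% | 4.1 points | 44% | 4.2 points |

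**4. Wider assumptions.** Take s of 5–30% and uptake u of 10–60% among regular clients. Let uptake in one-visit clients be equal to u or half of it, and receipt be 20% without and 60–90% with the consultation. Then shift = share × (1 − u) × (receipt with − receipt without).

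- Smallest (s = 5%, u = 10%, half uptake, 60% receipt): share 0.3%, shift 0.1 points.
- Middle (s = 10%, u = 40%, equal uptake): share 4.3%, shift 0.043 × 0.6 × 0.4 = 1.0 points to 0.043 × 0.6 × 0.7 = 1.8 points.
- Largest (s = 30%, u = 40%, equal uptake, 90% receipt): share 14.6%, shift 0.146 × 0.6 × 0.7 = 6.1 points.

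**5. Baseline.** No healthy choices consultation exists before the intervention, so the baseline survey is not exposed.

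**The case against.** The strongest reply is that a consultation in this article ordinarily means a usual one. Section 2.1 describes care as consultations with an allocated clinician. The tested contact carries its own name throughout, and section 2.6.3 speaks of community mental health appointments. At baseline the rule can only mean usual consultations, so the same meaning at follow-up is natural. The HCC enters a summary in the record, and how it is logged is undecided, so it may never appear as a countable attendance. Which appointment codes count is also the kind of detail that a fuller protocol may settle.

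This makes the risk conditional, and that part of the reply stands. It does not close the gap. The article does state the rule, and nothing in it excludes HCC contacts. The cohort rule shows the authors adding the qualifier when they want it. The sentence "Participation in data collection will be independent of any care provided by the service" concerns taking part in the surveys and does not define which contacts count.

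A reader might infer more than the documents support:

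- *That the healthy choices consultation alone satisfies the rule.* It supplies one of the two contacts; a usual consultation is still needed. Only clients with exactly one usual consultation are affected.
- *That the primary outcomes are biased as a matter of fact.* That depends on how HCC contacts are logged and extracted, which is not stated.
- *That the shift could reach about 7 points in the step 3 scenarios.* This comes from 11.8% × (80% − 20%) = 7.1, which holds the rest of the intervention sample at 20% as if no regular client attended the HCC. With 40% uptake the rest would be near 44%.
- *That a benefit could be created from nothing.* If the consultation did not raise reported care, admitting these clients would not by itself produce a difference. The mechanism inflates a real effect. One-visit clients may also attend the HCC less often or receive less usual preventive care, which would reduce the shift.

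**Conclusion.** The point holds as a conditional weakness of the follow-up entry rule. As written, the rule permits a count in which eligibility differs by arm because of the tested care, and the direction would favour the intervention. Whether it happens depends on the logging and extraction of HCC contacts.

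The size cannot be derived from the documents. Under the stated assumptions it is about 1 to 4 points, and 0.1 to 6.1 points over the wider grid, against a 25-point target. That would inflate the estimate rather than decide the trial's conclusion by itself. The change is still worth making, because it is cheap and adjustment for the listed covariates would not remove the selection.

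**What to change.** State in the entry rule that the two qualifying consultations are usual mental health consultations, excluding contacts with the HCC. Apply this in both arms; it makes a difference only at follow-up. Apply the same exclusion to the 9-month appointment count extracted from the records.

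If the follow-up sample has already been drawn, add a sensitivity analysis of the primary outcomes restricted to clients with at least two usual consultations, identified from the extracted records.

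Cost: HCC contacts must be identifiable in the records, which should be settled when co-development decides how they are logged. A few clients whose second contact was with the HCC will not be sampled. The planned 180 clients per arm and the power are unchanged.
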